### Post meeting agenda

Sending out the summary of the meeting and the Commitment Contract to the PI to sign and send back to the Trial OfficeSending out a text message every Monday to the PI and research nurse during the whole period as a friendly reminder

### Refusing to participate in the study

If a centre refuses to participate in the study, the reason for this is noted. We will include the centre as ‘intention-to-treat’.

### Sample size and randomisation

The study has been running for almost 3 years and we know the recruitment rate per centre and month. Among the 32 centres in EFFECTS, we have identified five centres that have achieved our goal, i.e. recruiting two or more patients per month. These are the top recruiters (Danderyd, Karolinska Solna, Skövde, Sundsvall and Mora). We will not intervene with these centres because we believe that they have reached their full potential and the intervention is too weak for them. Not including the top recruiters leaves us with 27 centres in this study.

### Blinding

The participants in the EFFECTS study are not aware of the embedded study. We will not mention the intervention or in what order we will do the intervention outside the group responsible for ERUTECC. For obvious reasons, there is no blinding of the intervention. The centres will not be informed that we are measuring numbers of randomised patients before and after the teleconference, but they are fully aware that we want to enhance recruitment. The exact numbers of recruitments per centre has been available in the public domain through a link that has been updated in real time since the start of the EFFECTS study.

### Statistical methods

We will compare the numbers of included individuals 60 days before the teleconference with the numbers of subjects 60 days post intervention. The null hypothesis is that there will be no difference before and after. We consider a 20% increase in recruitment rate as clinical relevant, although it is arbitrarily chosen.

Statistical example:Sixty days pre-teleconference: 60 individualsSixty days post-teleconference: 78 individualsThat is, 78/60 = 1.3; a 30% increase in recruitment

In EFFECTS, we have a screening list in which we note all eligible individuals who have been considered as candidates for EFFECTS. If these patients are not part of the study, the reason is noted. Usually the reasons are administrative and non-willingness. We will compare the numbers of randomised patients with the eligible patients on the screening list.

The outcome of the study is the number of included patients per centre. Inclusion is available through our electronic randomisation system, and we will keep a separate log for every teleconference. If a centre refuses to be part of ERUTECC, we will still include the centre in the analysis (intention-to-treat). In addition, we will also do a ‘per-protocol analysis’.

### Planned subgroup analyses:

Are there any differences in recruitment rate between a medium recruiting centre versus a low recruiting centre?To what extent does the size of the stroke unit contribute to the number and percentage of patients included? Are there any differences between large stroke units versus small stroke units?Are there any differences between stroke units versus rehabilitation centres?Are there any differences between university hospitals versus non-university hospitals?Are there any differences between experienced centres versus non-experienced centres?

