**Fig. 3 Fig3:**
[figure not shown]
The flow of participants in the ERUTECC study. In ERUTECC, each centre follows the same flow, with a 60-day period of running in, and a 60-day post-intervention period (teleconference). The figure shows one step. We will add up all patients for all 11 steps in the 60-day running-in period and compare this with the inclusion rate for all centres’ 60-day post randomisation period

In ERUTECC, all centres have a 60-day running-in period and a 60-day post-intervention period. Our plan is to start in September 2017 and finish in October 2018.

The 27 sites will be divided into two categories: medium and low recruiters. The rationale for this is that we do not want to risk all medium recruiters falling into the same step, for example the summer period, which usually a low-recruiting period. The centre will be randomised in terms of the order in which intervention will be performed, leading to (at least) one medium and (at least) one low recruiter in each of the 11 steps (Fig. 2).

All centres in the EFFECTS study, their classification, type and numbers of patients are listed in Table 1.

**Table 1 Tab1:** Centres in EFFECTS as of 31 August 2017

Centre	Type of centre	Number of stroke patients per year^a^	First included patient in EFFECTS (yyyy-mm-dd)	Total number of patients recruited	Percentage of number of patients recruited^b^
01 Danderyd Hospital	SU at hosp	837	11/11/2014	110	14%
02 Karolinska University Hospital Solna	SU at univ hosp	542	10/20/2014	98	12%
03 Skaraborg Hospital Skövde	SU at hosp	422	10/20/2014	56	7%
04 Hässleholm Hospital	SU at hosp	203	3/23/2015	32	4%
05 Uppsala University Hospital	SU at univ hosp	496	4/20/2015	39	5%
06 Karolinska University Hospital Huddinge	SU at univ hosp	488	4/8/2015	15	2%
07 Mora General Hospital	SU at hosp	226	4/15/2015	49	6%
08 Falu General Hospital	SU at hosp	510	5/13/2015	12	1%
09 Lidköping	SU at hosp	162	10/6/2015	12	1%
10 Capio St Göran’s	SU at hosp	697	6/24/2015	51	6%
11 Visby General Hospital	SU at hosp	132	11/4/2015	7	1%
12 Norrland University Hospital	SU at univ hosp	355	9/22/2015	12	1%
13 Kristianstad Central Hospital	SU at hosp	334	9/24/2015	11	1%
14 Norrtälje Hospital	SU at hosp	165	12/9/2015	1	0%
15 Helsingborg General Hospital	SU at hosp	391	11/18/2015	15	2%
16 Skåne University Hospital Malmö	SU at univ hosp	478	12/18/2015	16	2%
17 Halland Hospital Halmstad	SU at hosp	374	12/1/2015	36	4%
18 Mälar Hospital Eskilstuna	SU at hosp	246	2015-22-23	10	1%

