19 Rehab Station Stockholm	Neuro RH	^c^	11/24/2015	4	0%
20 Skåne University Hospital Lund	SU at univ hosp	634	2/29/2016	9	1%
21 Sundsvall Hospital	SU at hosp	486	12/18/2015	66	8%
22 Sahlgrenska University Hospital	SU at univ hosp	789	4/15/2015	16	2%
23 Högsbo Rehabilitation Hospital	Neuro RH	^c^	3/4/2016	2	0%
24 Stora Sköndal Neurological Rehabilitation Clinic	Neuro RH	^c^	1/22/2016	13	2%
25 Östersund Hospital	SU at hosp	339	3/10/2016	21	3%
26 Alingsås General Hospital	SU at hosp	223	2/25/2016	34	4%
27 Ängelholm Hospital	SU at hosp	232	3/15/2016	16	2%
28 Stockholm Nursing Home	Neuro RH	^c^	4/4/2016	13	2%
29 Örebro Rehabilitation Clinic	Neuro RUH	^c^	10/10/2016	10	1%
30 Norra Älvsborg County Hospital Trollhättan	SU at hosp	699	12/3/2016	4	0%
31 Bromma Geriatric Clinic	Ger RH	^c^	11/24/2016	1	0%
32 Västmanland Hospital Västerås	SU at hosp	411	1/18/2017	9	1%
33 Dalen Hospital	Ger RH	^c^	5/22/2017	2	0%
34 Lindesberg General Hospital	SU at hosp	117	6/15/2017	2	0%
35 Hudiksvall Hospital	SU at hosp	187	4/12/2017	6	1%
Total				810	100%

The centres are numbered in the order they were initiated. Closed centre denotes that the centre is closed for EFFECTS and not included for ERUTECC. *Abbreviations: SU at hosp* Stroke unit at hospital, *SU at univ hosp* Stroke unit at university hospital, *Neuro RH* Neurological rehabilitation hospital, *Neuro RHU* Neurological university hospital, *Ger RH* Geriatric rehabilitation hospital

^a^Numbers of patients in the stroke unit according to the National Swedish Quality Register [19]

^b^Number of patients included divided by total number of stroke patients during active participating time the EFFECTS study as of 31 August 2017

^c^Rehabilitation hospitals/units. The exact number of stroke is not part of the Riksstroke statistics

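### Stroke-unit size, a number in Table 1 for the 21 retained stroke units, is to be compared as large versus small; a continuous term would keep the quarter to a third of the information that a fairly central split loses

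*Protocol article*

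**What the plan says.** The Planned subgroup analyses section treats unit size in two sentences. The first is open: "To what extent does the size of the stroke unit contribute to the number and percentage of patients included". The second fixes a two-group contrast: "Are there any differences between large stroke units versus small stroke units". The last item in the section is also a two-group contrast: "Are there any differences between experienced centres versus non-experienced centres".

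Table 1 has a column headed "Number of stroke patients per year", with the footnote "Numbers of patients in the stroke unit according to the National Swedish Quality Register". For the rehabilitation centres a further footnote explains the blank: "The exact number of stroke is not part of the Riksstroke statistics". Table 1 also lists each centre's date of first inclusion and total recruited. No column is labelled experience, and the article does not define the term.

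The Limitations section says that there will be several subgroup analyses and that they call for cautious reading.

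**The concern.** Unit size is already held as a number. Reducing it to two groups treats a unit with 117 stroke patients a year like one with 246, and a unit with 411 like one with 789. With only 21 units the analysis is weak to begin with, and the split makes it weaker. The answer also depends on where the line falls: moving it from 250 to 500 cuts the large group from 13 units to 5.

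What is at stake is the usefulness of one exploratory question, namely whether the teleconference and contract work differently in larger and smaller units. The main before/after comparison does not depend on it.

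**Working it through.** **The plan's own count.** 35 initiated centres − 3 closed − 5 top recruiters = 27, as the article states. Six of the 27 are rehabilitation centres with no register figure, which leaves 21 stroke units. The article gives no figure for the subgroup analyses themselves, so there is none to reproduce.

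**Inputs from Table 1.**
- Annual stroke patients at the 21 units: 117, 162, 165, 187, 203, 223, 232, 246, 334, 339, 355, 374, 391, 411, 478, 496, 510, 634, 697, 699, 789. The median is 355.
- Expected inclusions per 60 days for each centre = 60 × total recruited / days from first inclusion to 31 August 2017. The 27 centres recruited 407 patients, which gives 43.7 per 60 days; the 21 stroke units give 37.2.
- Assumption: the unreadable date of centre 18 is taken as 23 December 2015.

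**Formula.** If the effect is linear in x = log(annual stroke patients), a two-group split keeps a share of the information equal to the squared correlation between x and the split indicator:

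share kept = p(1 − p)d² / V

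Here p is the share of expected inclusions in the large group, d is the difference in mean log size between the groups, and V is the variance of log size. All are weighted by expected 60-day inclusions, and V = 0.2512.

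| Large means more than | Large units | p | d | Share kept | Loss |
|---|---|---|---|---|---|
| 250 | 13 of 21 | 0.628 | 0.890 | 0.737 | 26% |
| 355 (median) | 10 of 21 | 0.513 | 0.832 | 0.688 | 31% |
| 400 | 8 of 21 | 0.385 | 0.821 | 0.636 | 36% |
| 500 | 5 of 21 | 0.206 | 0.863 | 0.485 | 51% |

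For the cut at 400: 0.385 × 0.615 × 0.821² / 0.2512 = 0.636.

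**Sensitivity.**
- With every unit weighted equally, the shares kept are 0.745, 0.685, 0.644 and 0.510, so the weighting matters little.
- If the effect were linear in size itself and not in its logarithm, the weighted losses at the four cuts would be 40%, 36%, 31% and 33%. The pattern across cuts changes, but the loss remains material.
- In theory, a median split loses 36% for a normal variable and 25% for a uniform one.

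**What the cut does to the groups.** Expected pre-window inclusions in the large group are 0.628 × 37.2 = 23.4 with a cut at 250, and 0.206 × 37.2 = 7.7 with a cut at 500.

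**In terms of power.** The article states no power or alpha for this question. Suppose, for illustration only, 80% power for the continuous term at two-sided 0.05. The split then has power Φ(2.80 × √share − 1.96): 67% at 250, 64% at 355, 61% at 400 and 50% at 500.

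**Experience, if it means time in EFFECTS.** Months from first inclusion to 31 August 2017 run from 2.5 to 29.3 over the 27 centres. Weighted in the same way, splits at 12, 18 and 24 months keep 76%, 64% and 46%. The last leaves only 5 centres on the longer side.

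**The case against.** The strongest reply is that the open question on size comes immediately before the large/small question, so a full-scale analysis is already possible and the split may be only a companion display. This stands in part: the article does not confine size to two groups. But the open question asks how size relates to the number and percentage of patients included. It does not replace the large/small contrast, which is listed as a planned comparison in its own right.

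Several stronger readings are tempting, and the documents do not support them.
- *That half the information is lost.* On the log scale this needs a lopsided cut such as 500. The article proposes no cut at all.
- *That the split will be chosen after the data are seen.* The article gives no cut-off, and the Blinding section says that centre counts are public. However, a cut-off is commonly left to an analysis plan or full protocol, and neither is shown. Nothing says when the groups would be formed.
- *That experience is a measured scale being thrown away.* Time since first inclusion is only one possible meaning. Total recruited or earlier trial work are others.
- *That no natural gap could settle a split.* Months since first inclusion show a clear gap between 10.7 and 16.9, dividing the centres 7 versus 20. Size has a gap from 246 to 334 (8 versus 13 units) but also one from 510 to 634, so it has no single obvious dividing point.

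It is also fair to say that a continuous term rests on an approximately linear trend, and that the article already urges caution about these analyses. Caution in reading does not recover lost information.

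**Conclusion.** The point holds in a limited form, and it is minor. The article plans a two-group contrast for a variable that it holds as a number at 21 units. With an effect roughly linear in log size, a fairly central split gives up about a quarter to a third of the information (26% to 36% for cuts from 250 to 400), and more only if the groups are very unequal. This rests on the linear trend, on Table 1 average rates as weights, and on the assumed date for centre 18; the last two have little influence on the result for size. The same reasoning extends to experience only if that word means time in EFFECTS.

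The objection is to the form of the contrast, not to the absence of a cut-off, so it would stand even if an unseen plan names one. The analyses are exploratory in character and the primary comparison is untouched.

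**What to change.** In Planned subgroup analyses, state that unit size will be analysed with log(annual stroke patients) from Table 1 as a continuous modifier of each centre's post/pre change, in the 21 stroke units with a register figure. Keep large versus small only as a descriptive table, split at the Table 1 median (355, with the unit at the median assigned in advance to the small group: 10 versus 11 units).

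Define 'experienced'. If it means time in EFFECTS, use months from first inclusion to 31 August 2017 in the same way for the 27 centres, after correcting the date of centre 18.

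The cost is a change of wording. The size variable is already tabulated and no new data are needed beyond the one corrected date. The small downside is the assumption of an approximately linear trend, which the descriptive table lets a reader check roughly.

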### Recruitment

We aim to start this study in September 2017. At that time, we will have 27 active centres, not including the five top recruiters.

### Explanation of the randomised, stepped-wedge design

Step 1 starts with a 60-day running-in period beginning in September 2017, and consists of at least one medium and one low recruiting centre. The teleconference is performed at the end of October 2017, and the observation follows 60 days post interventionStep 2 starts with a 60-day running-in period beginning in October 2017, and consists of at least one medium and one low recruiting centre. The teleconference is performed at the end of November 2017, and the observation follows 60 days post intervention

### Harm

It is hard to anticipate any harm from ERUTECC. The host trial, EFFECTS, has specific monitoring performed by the Karolinska Trial Alliance. The monitor is independent and the Karolinska Trial Alliance follows a specific monitor plan, which, for example, checks every patient consent. The participants in ERUTECC will received no extra benefits for being part of the study and there will be no compensation for those who claim that they have suffered harm from trial participation.

### Problems

Anticipated problems.It is possible that the intervention will develop during the course of the study. At the beginning we will have a clear agenda, but it is possible that we will learn through the process, and that the intervention will become a little differentIt is also possible that the participants at the centres that have not yet been intervened with will find out about the interventions and will change their pattern of behaviour before the intervention takes placeThe organisation of the intervention will be challenging because it involves more than 27 centres over a period of 1 yearAt some centres, the head of the department will not be able to join during the structured telephone conferenceIt is possible some centres will refuse to be a part of the intervention and this will interfere with the results

## Discussion and generalisability

EFFECTS is a pragmatic study of stroke and the largest RCT study of stroke in Sweden. The result from this embedded study could probably be generalised to high-income countries, like Sweden. The result could be useful in clinical settings outside the field of stroke, and if our study is positive, the results could be applicable to a wide range of RCT studies. The study will add knowledge about the management of RCT studies and recruitment.

### Limitations

One limitation is that we will not include the top recruiters. However, we believe that the high recruiting centres have reached their maximum level of recruitment and the intervention will only have a minor effectIt is possible that the intervention is too weak to have positive results. After all, we are trying to change the pattern of behaviour for over 60 persons and behaviour change is one of the hardest things to accomplishSince we started the EFFECTS study, we have already tried different things to identify barriers and find ways to enhance recruitment, so it may be that there is nothing more to be doneWe are planning to carry out multiple sub-group analyses. The results must be interpreted with caution

## Trial status

The main study – EFFECTS – included its first patient on 20 October 2014, and as of 31 October 2017, 881 patients have been included. The last patient is estimated to be recruited in March 2019, with the last follow-up 1 year later. The ERUTECC will start in November 2017 (Fig. 2) and continue for 1 year.

## Abbreviations

CONSORT: Consolidated Standards of Reporting Trials
EFFECTS: Efficacy oF Fluoxetine – a randomisEd Controlled Trial in Stroke
ERUTECC: Enhancing Recruitment Using Teleconference and Commitment Contract
RCT: Randomised controlled trial
SPIRIT: Standard Protocol Items: Recommendations for Interventional Trials
SWAT: Study Within a Trial repository
